### Missing data

Retention of participants will be ensured during the monitoring period through the support of mothers, lactation encouragement and provision of psychological services. The following events are considered as follow-up losses: the study is not continued due to neonatal death, unstable clinical symptoms and other reasons; the intervention dose does not reach the expected 70%; and parents of preterm infants withdraws from the trial at any time. Eliminated or corrected observations and related reasons will be recorded for future reference.

Most types of missing data in the study will come from random missing. All missing data will be processed with SAS software using the double-robust inverse probability weighting method [53]. Its underlying principle is to estimate the weighted average of the outcome indicators of the complete data sample. Among them, the weight of each individual is the reciprocal of the probability that the outcome index of the individual is not missing, yielding an effect estimation closer to the real value.

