In the first 48–72 h the treatment group will receive the treatment measures: two 1 mL sterile syringes each aspirated with 0.1 mL of colostrum, placed at room temperature for 5 min. The colostrum will be maintained at room temperature for OAC use. After removing the tip and cap of the first syringe, the colostrum will be slowly injected along the right oral mucosa for at least 20 s. Then, the right buccal mucosa will be wiped with a sterile cotton swab for at least 10 s. The second syringe will be used in the same way on the left oral mucosa. The procedure will be performed every three hours for five days. The control group will be treated with sterile water following similar operation steps. Colostrum for the control group will be frozen in the NICU breast milk refrigerator for enteral feeding. Vital signs will be monitored throughout the process, including heart rate, respiration, body temperature and pulse oxygen saturation. During treatment, newborns will be regularly monitored and observed. If their clinical symptoms are unstable (heart rate is greater than 200 or less than 100, breathing is greater than 80, or the oxygen saturation is maintained above 85% only when the oxygen concentration increases by 10%) [44], the intervention will be interrupted. Once the clinical situation stabilizes, the treatment will be resumed immediately, and the final intervention dose and adverse reactions recorded.

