### Statistical analysis

Intention to treat (ITT) method will be used for statistical analysis. Baseline maternal and infant demographic and clinical characteristics of OAC group and placebo group will be compared using chi-square or Fisher’s exact test (such as infant sex, mode of delivery and presence or absence of chorioamnionitis) and t-test or Wilcoxon test for continuous variables. After removing low-quality sequences, original data will be analyzed following the steps of 16S rRNA discovery, clustering and identification. The number of operational taxonomic units (OTUs) will be calculated for each sample at a 97% sequence similarity level. A specific taxonomic unit will represent a specific species. Subsequently, a sparse curve will be drawn based on the results of OTUs generated using sample sequencing. Wilcoxon test will be used to analyze the diversity and richness of microbiota within individuals. A t-test or Wilcoxon test will be used to compare alpha diversity (Shannon index, Simpson index, and Chao1 index) between the two groups of infants with and without OAC intervention within four weeks of birth. Repeated measures analysis of variance (ANOVA) (for normally distributed data) or Kruskal Wallis test (for non-normal data) will be used to evaluate the microbial alpha diversity at different time points. The proportion difference of gut microbiota at the phylum and genus levels will be calculated using chi-square or Fisher's exact test. Values with *p* < 0.05 will be considered statistically significant. Beta diversity will be calculated using the Vegan package, and a principal co-ordinates analysis (PCOA) based on Bray–Curtis distances will be plotted. Adonis permutational multivariate analysis of variance of Bray–Curtis distances with 9999 permutations will be used to compare microbial community structure between each of the two groups.

Redundancy analysis (RDA) will be performed using the Vegan package to define the factors that could significantly affect gut microbial composition in each group. We will use Linear discriminant analysis (LDA) of effect size (LEfSe) to determine the most discriminant taxa between the two groups. If the effect of OAC intervention on gut microbiota is less than that of other confounding factors (delivery mode, antibiotic use, feeding type, etc.), we will adjust it with RDA.

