### Participant recruitment and informed consent

Data collection will begin in October 2022 and is expected to end in September 2023. Shenzhen People’s Hospital is the pilot research unit, and the pilot research will be carried out from August to September 2022. The annual census of very preterm infants in this facility is relatively high and the breastfeeding rate is very high (above 80%), hence ideal for the recruitment of subjects. Mothers who meet the inclusion criteria (fetal weight < 1500 g estimated by ultrasound) will be invited to participate. To achieve full registration of participants and target sample size, breast-feeding education will be provided in obstetrics to improve lactation awareness. Professional staff will guide pregnant women and provide them with breast care (such as breast massage). The principal investigator (PI) will explain the study in detail and respond to any questions raised. Mothers will be informed of their right to withdraw from the intervention at any time. They will also be informed that if they decline to participate in the study, their care and that of their infants will not be affected.

Written informed consent will be obtained from the patient's guardian. This study complies with the Declaration of Helsinki.

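### Counting infants who receive under 70% of the intended dose as follow-up losses contradicts the stated ITT analysis and can remove infants unequally by arm

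*Protocol article*

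**What the plan says.** The Statistical analysis section sets the principle: "Intention to treat (ITT) method will be used for statistical analysis".

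The Missing data section lists three kinds of follow-up loss:
- participation ends: "the study is not continued due to neonatal death, unstable clinical symptoms and other reasons";
- "the intervention dose does not reach the expected 70" per cent;
- the parents withdraw the infant.

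The same section refers to eliminated observations, expects that "Most types of missing data in the study will come from random missing", and states that "All missing data will be processed with SAS software using the double-robust inverse probability weighting method". It describes the weight as the reciprocal of the probability that an infant's outcome is not missing.

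The Sample size section raises 143 per group to 160 to allow for 10–12% loss to follow-up. Under Outcomes, both primary measures (Shannon index and short chain fatty acids) are taken from the day-7 stool.

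**The concern.** The dose an infant received is a matter of adherence. It does not determine whether a stool was collected on day 7. Defining loss by dose turns a per-protocol criterion into a missing-data label, and the ITT statement and the loss definition cannot then both be followed.

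Two things are at stake. First, the estimand changes. If under-dosed infants are treated as missing and the rest are reweighted, the result targets at best the effect had every infant reached 70% dosing, under a missing-at-random assumption, instead of the effect of assignment.

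Second, reaching 70% is a post-randomisation event whose causes are not the same in the two arms. Colostrum doses need the infant's own mother's milk (the procedure section asks for at least 1.6 ml), while control doses are sterile water. A supply shortfall can therefore produce a loss only in the colostrum arm. The article itself connects lactation with retention, in the Missing data section and again under Quality control. Milk supply may also go with later feeding type, which the article names as a confounder of the microbiota.

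**Working it through.** **Dose threshold.** The procedure is given every 3 hours for 5 days: 24/3 = 8 doses a day, and 8 × 5 = 40 doses. 70% of 40 is 28. By volume, 40 × 0.2 ml = 8.0 ml, and 70% is 5.6 ml. An infant given 27 doses is a loss under the rule, even with a day-7 stool in the freezer.

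**The plan's own figures.** Difference 0.2, SD 0.6, 80% power, two-sided 0.05. The two-sample t-test solution is 142.25, rounded up to 143 per group, as stated. Inflation: 143/(1 − 0.10) = 158.9 and 143/(1 − 0.12) = 162.5. The stated 160 corresponds to a loss of 1 − 143/160 = 10.6%. The sample size reproduces, so nothing here rests on an arithmetic error. It also shows that losses are planned as infants who do not contribute to the 143 analysed.

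**Size of a possible bias.** The article gives no exclusion rates and no outcome difference between excluded and retained infants, so the following inputs are assumptions. Let a share q of an arm be excluded, with a mean Shannon index lower by g than that of retained infants. The retained mean then exceeds the full-arm mean by q × g. With no true effect:

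- bias = g × (q_OAC − q_control)
- SE = 0.6 × √(1/n_OAC + 1/n_control), where n = 160 × (1 − q)
- type I error = P(Z > 1.96 − bias/SE) + P(Z < −1.96 − bias/SE)

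For 15% against 5% excluded, n = 136 and 152, and SE = 0.6 × √(1/136 + 1/152) = 0.0708.

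| Excluded, OAC v control | g | Bias | Share of 0.2 | Type I error |
|---|---|---|---|---|
| 12% v 12% | 0.2–0.6 | 0 | 0% | 5.0% |
| 10% v 5% | 0.2–0.6 | 0.01–0.03 | 5–15% | 5.2–7.1% |
| 15% v 5% | 0.2 | 0.02 | 10% | 5.9% |
| 15% v 5% | 0.4 | 0.04 | 20% | 8.7% |
| 15% v 5% | 0.6 | 0.06 | 30% | 13.5% |

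The table gives no credit for any correction by the doubly robust weighting, so it describes the unweighted comparison of retained infants.

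**Power if every infant is kept.** Suppose a share of colostrum infants gets no effect (again an assumption). With 160 per arm analysed, SE = 0.6 × √(2/160) = 0.0671.
- No dilution: 0.2/0.0671 = 2.98, power 0.846.
- 10% without effect: difference 0.18, 0.18/0.0671 = 2.68, power 0.765; 175 per arm would be needed for 80%.
- 20% without effect: difference 0.16, power 0.665; 221 per arm would be needed.

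These counts exclude any allowance for stools truly not obtained.

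**The case against.** The best defence is that the article never says outright that stools from under-dosed infants are thrown away. It defines the weight by whether the outcome is available, not by dose, so a team could keep those infants and weight only for absent samples. That makes the text ambiguous. It does not remove the contradiction, because the dose item is listed as a loss under Missing data and the sample size is inflated for losses.

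A reader might infer several stronger points that the documents do not support:

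- *That any infant who becomes unstable is lost, in conflict with the dosing procedure.* Instability counts only where participation is not continued. The procedure section has dosing interrupted, and then "Once the clinical situation stabilizes, the treatment will be resumed immediately". The two are compatible. An interruption matters here only if it ends participation or takes the infant below 70%.
- *That colostrum infants will in fact be lost more often.* No rate by arm is given. The breastfeeding rate above 80% is a general figure for the coordinating hospital, not a rate of failing 28 of 40 doses. Mothers with contraindications to breastfeeding are excluded, lactation support is planned, and only about 1.6 ml a day is needed. Instability, death and withdrawal can occur in both arms, with the intervention nurses blinded. What stands is that supply shortfall is possible in one arm only.
- *That deaths are declared missing at random.* The article says this of most types of missing data and does not classify deaths. It does list them as losses and send all missing data to weighting.
- *That the error rate could approach 40%.* This needs 20% against 0% exclusion together with a deficit of 0.6 (39.2% by the formula above). The direction of the deficit is also an assumption, and weighting on the illness and feeding data that are collected could recover part of any bias.

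**Conclusion.** The point holds for the dose criterion. A post-randomisation adherence threshold is used to define follow-up loss while the analysis is called ITT, and the two passages must be reconciled because they decide who enters both primary comparisons. This contradiction does not depend on any assumed rate.

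The size of the harm does. At 15% against 5% exclusion with a deficit of 0.2 to 0.6, the bias is 10 to 30% of the design difference and the type I error about 6 to 13.5%. With equal exclusion of similar infants there is none. The documents support saying that the rule can remove infants differentially, and no more than that.

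**What to change.** Reword the Missing data section before unblinding:

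1. Remove the 70%-dose item from the definition of follow-up loss. Limit loss to outcomes truly not obtained. An infant whose dosing or participation stopped is not a loss if a stool exists and consent allows its use.
2. State that the primary analysis includes every randomised infant with a day-7 stool, in the assigned arm, whatever dose was received.
3. Apply the weighting only to absent day-7 outcomes.
4. Use the 70% threshold only to define a secondary per-protocol set.
5. Report deaths before day 7 by arm.

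The wording costs one paragraph and no new data collection. The statistical cost is dilution: if 10% of colostrum infants got no effect, power with 160 per arm analysed would be about 0.77 instead of 0.85. The 10–12% allowance should then cover absent samples only, and dilution should be considered in the assumed difference. The primary analysis would still rely on a missing-at-random assumption for stools not obtained.

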### Data management

The purpose of data management is to ensure the reliability, integrity and accuracy of data. All study participants will be given a study identification number. Data from each research center will be imported to the collected electronic data capture (EDC) system and protected by password. These data will be verified, corrected, blind audited and locked. The backup is scheduled at midnight every day. Shenzhen People’s Hospital, as the supervision unit, will provide a detailed definition of each variable in the EDC system and ensure consistent data entry. The research team's access to participant information will be strictly limited to the purpose of running the study. In future studies, the storage and use of these data will require additional consent of both parents. For this analysis, the researchers will have access to the finalized test data set.

### Quality control

In clinical research, quality control should be carried out in the whole process of trial design, implementation and completion. In the design stage, to improve the quality of test data, a data monitoring committee (DMC) will be established. DMC will composed of the data verifiers (ZY and NW) and the principal investigators at each center (XY, RL and HP). The research team at each center will be composed of the principal investigator (XY, RL and HP), data quality controller (CC, LZ and ZY), syringe preparing nurse and the intervener. In the design phase, calculation of sample size, training of researchers, formulation of data management plan, and reasonable selection of efficacy observation indicators will be considered. The training will cover standardized operation process, including recruitment, randomization and web-based data collection. In the implementation phase, a standardized data collection process will be adopted, and the DMC will conduct regular verification of the filling of case report form (CRF) and research records at each center. Data verification will mainly focus on the following aspects: 1) the timeliness and completeness of data filling in CRFs, and the education on mother lactation to minimize data loss; 2) normalization of data filling; 3) records of adverse events, including the number and duration of adverse events during OAC, and records of colostrum intervention; and 4) monitor the progress of the study and verify the implementation of the study protocol, blind method performance and adverse events. After the study, the data will be collated, verified and statistically analyzed (including missing values, inclusion and exclusion criteria, and adverse events). The quality control process of the protocol is shown in Fig. 2.

**Fig. 2 Fig2:**
[figure not shown]
Quality control process of the protocol. DMC, data monitoring committee (composed of data verifiers at the coordination center and the principal investigators at each center); CRF, case report form. * The research team of each center is composed of the principal investigator, data quality controller, syringe preparing nurse and the intervener. ** The trial steering committee (composed of the directors of neonatal pediatrics at each center and the heads of the medical safety review team)

The whole research team will hold online meetings every month through multimedia video conferencing software to discuss the implementation of the scheme as needed and quickly solve any problems. When 50% of randomly assigned patients completed five stool samples collection, the primary endpoint was analyzed in the interim. An interim-analysis will be conducted by independent statisticians without knowledge of treatment allocation. Statisticians will report to the DMC. The DMC will conduct non-blind access to all data and discuss the results of the interim analysis, adverse events and compliance with the trial steering committee (composed of the directors of neonatal pediatrics at each center and the heads of the medical safety review team) at the multicenter meeting. Adverse events are defined as aspiration to the lungs, resuscitation due to severe bradycardia or apnea after intervention, and postnatal infection with cytomegalovirus thought to be associated with fresh breast milk. If cases related to these adverse events occur, we will intervene immediately. To ensure the safety of the included infants, vital signs will be carefully monitored during oropharyngeal administration. If the vital signs are unstable, the intervention will be stopped in time. The trial steering committee will decide to continue the trial and report to the ethics committee, which is independent of the sponsor and investigators (Fig. 2).

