### Randomization

A 1:1 block randomization scheme will be adopted. Each group will be stratified by birth gestational age (< 28 weeks, 28 weeks, and 32 weeks). A random serial number will be randomly generated for each layer using SAS (v9.4 SAS Inst. Inc., Cary, NC) before the start of the study. The block length will be 6. Statisticians will prepare sealed, numbered, opaque envelopes for each site and hand them over to the study coordinator, who will ensure that the envelopes are used in a numerical order. After receiving the notice, the study coordinator will open the envelope, take down the group assignment form, copy the form and send it to the statistician. The manuscript will be left in the case file of the preterm infant. To achieve blinding, the study coordinator preparing the syringe (colostrum or placebo) will be different from the nurse conducting the intervention. The subjects, intervention nurses, the principal investigator and the data verifier will be blinded. During the pilot test, non-fixed codes will be used for blinding to represent each allocation scheme to prevent unblinding by inadvertently losing blindness to all trial participants.

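### The data monitoring committee given unblinded interim data is made up of the principal investigators and data verifiers whom the protocol declares blinded

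*Protocol article*

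**What the plan says.** **Who is blinded.** The Randomization section of the protocol article states: "The subjects, intervention nurses, the principal investigator and the data verifier will be blinded". The person who prepares the syringe is kept separate from the nurse who gives it, so the preparer is the one role that must know the arm.

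**Who sits on the DMC.** The Quality control text and the Fig. 2 legend agree on the membership: "data monitoring committee (composed of data verifiers at the coordination center and the principal investigators at each center". The text identifies two data verifiers and three principal investigators, and no other member.

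**What the DMC sees, and when.** The text after Fig. 2 sets the interim: "When 50% of randomly assigned patients completed five stool samples collection, the primary endpoint was analyzed in the interim". On who performs it: "An interim-analysis will be conducted by independent statisticians without knowledge of treatment allocation". These statisticians report to the DMC, and then: "The DMC will conduct non-blind access to all data and discuss the results of the interim analysis". The discussion partner is the trial steering committee, which includes the neonatal directors of the three centres.

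**Where the allocation form goes.** In the Randomization section the study coordinator opens the envelope and sends a copy of the form to the statistician. Then: "The manuscript will be left in the case file of the preterm infant".

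**The concern.** The roles named as blinded in one section are the roles given unblinded access in another, while the trial is still running. This is a contradiction in the current text, not detail left to an analysis plan or a charter.

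The people concerned have influence over what happens next. Under Participant recruitment and informed consent, the principal investigator explains the study to mothers. Under Quality control, the principal investigators belong to the site research teams, and the DMC members regularly check case report forms and site records. Under Missing data, observations may be removed or corrected, and stopping for clinical instability or other reasons counts as loss to follow-up. Data management promises a blind audit before the database is locked. Knowledge of interim results by arm could colour how later infants are recruited, retained and cleaned.

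The case-file sentence adds a second possible leak. If staff who should be blinded can open that file, they can read the individual infant's arm.

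**Working it through.** The point is a textual conflict and rests on no calculated figure. The arithmetic below only sizes it.

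**Step 1: match the roles.**

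| Role | Randomization | Quality control and Fig. 2 |
|---|---|---|
| Principal investigator | blinded | DMC member, unblinded access to all data |
| Data verifier | blinded | DMC member, unblinded access to all data |
| Interim statisticians | not listed | do not know allocation, report to the DMC |
| Centre neonatal directors | not listed | discuss interim results with the DMC |

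Randomization uses the singular and Quality control the plural. No second, unblinded investigator or verifier is described anywhere, so the titles refer to the same roles. The blinded DMC roles and the unblinded DMC members therefore coincide: 3 + 2 = 5 people, the whole committee.

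**Step 2: check that the trial is still running.** The trigger is 50% of randomised infants with all five stools, the last on day 28. The Sample size section says the sample size will be adjusted on the interim results. Both place the unblinding before the end of enrolment.

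**Step 3: size it.** The planned total is 320 (160 per group). That figure is consistent with the plan's own inputs: 143 per group with 10.5% loss gives 143 / 0.895 = 159.8, or 160, within the stated 10–12%. I take the 50% as 50% of 320, no change in sample size, and even enrolment over one year.

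- Infants with complete sampling at the trigger: 0.5 × 320 = 160.
- Still to be enrolled or followed: 320 − 160 = 160. This is the upper bound.
- Randomised but not yet at day 28: 320 × 28 / 365 = 24.5, about 25.
- Not yet enrolled: 160 − 25 = 135.
- If 10–12% of the early infants never complete sampling, reaching 160 complete takes 160 / 0.90 = 178 to 160 / 0.88 = 182 randomised infants past day 28. Then 142 to 138 have not reached day 28, of whom about 117 to 113 are not yet enrolled.

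Sequencing and analysis time would lower these numbers further.

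**Step 4: the case file.** The sentence follows directly on "copy the form and send it to the statistician", so the manuscript can sensibly be read only as the original form. The same section specifies opaque sealed envelopes before opening, but states no seal or access limit for the form afterwards. Who may open the case file is not said.

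**The case against.** The strongest reply is that the damage is limited. Both primary outcomes are laboratory measurements, so unblinded investigators can hardly bias the assay. Infants past day 7 at the interim have already given their primary samples. Future allocations stay in sealed envelopes. Blinding of the subjects and the intervention nurses is untouched by the DMC arrangement. All of this stands. It narrows the consequence to recruitment, retention and data checking after the interim, but it does not reconcile the sections.

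Several stronger readings are tempting and are not supported:

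- **That the DMC decides the sample-size change.** The Sample size section names no decision-maker, and the decision to continue lies with the steering committee. The DMC receives and discusses the results, and no more than that is stated.
- **That the form copy sent to the statistician contradicts the blinded interim analysis.** That would need the two to be the same person. The interim statisticians are called independent, and nothing links them to the statistician who receives the copy.
- **That the case file exposes every infant from the first day.** The file could be a ward chart or a restricted research file. The text shows a possible leak, not an event.
- **That the unblinded investigators control feeding and antibiotics.** The Discussion names both as influences on the microbiota, but no section assigns these decisions to the principal investigators.
- **That no part of the double-blind description survives.** What fails is the stated blinding of investigators and verifiers, from the interim on.

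**Conclusion.** The contradiction is real and nothing else in the document resolves it. Followed as written, the plan unblinds all three site principal investigators and both data verifiers at the interim, although Randomization says these roles are blinded, and it carries the results to the centres' neonatal directors. At most about 160 infants would then still be enrolled or followed. About 113 to 135 of them would not yet be enrolled under even enrolment, depending on early losses and before laboratory time. These counts rest on the 50% referring to the planned 320 and on no increase in sample size. The direction and amount of any resulting bias cannot be derived from the document.

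The case-file sentence is a secondary point: a risk to blinding that the wording leaves open.

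This should be settled before the interim, because the sections cannot both be carried out and unblinding cannot be undone.

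**What to change.** Reconcile Randomization with Quality control and the text after Fig. 2:

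- Replace the sentence on unblinded access so that principal investigators, data verifiers and centre directors see only pooled or arm-coded interim data. The interim statisticians already work without allocation, so their reports can go forward in that form.
- If a decoded by-arm review is wanted, for efficacy or adverse events, limit it to people outside the blinded trial team and say who they are.
- Keep the original allocation form sealed with the study coordinator or syringe preparer, who already knows the arm, and not in the case file.

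The cost is protocol wording and a change in where one form is filed. A decoded review would also need reviewers from outside the team. The downside is that investigators lose sight of by-arm interim data. Arm-coded data can also hint at the arm if the groups differ clearly, so pooled data are the safer choice where they suffice.
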